## Abstract

**Background:**

Temperatures across Africa are expected to rise at up to twice the rate of mean global temperatures, posing significant health threats to vulnerable communities. Prolonged exposure to high day- and night-time temperatures has been implicated in a myriad of adverse health outcomes. The built environment and inadequate housing can exacerbate these consequences, prompting the need to evaluate heat adaptation interventions as a sustainable adaptation strategy for low-income and informal settlement dwellers. The Heat Adaptation Benefits for Vulnerable groups In Africa (HABVIA) study aims to assess the impact of passive cooling interventions in homes on several key physiologic and mental health outcomes, as well as building internal thermal conditions.

**Methods:**

HABVIA is a 3-year prospective controlled study to identify, implement and assess heat adaptation solutions in four low-income communities in one urban and one rural site in Ghana and South Africa, respectively. In each site, *N*=240 participants (*N*=60 per site) will be assigned to intervention or control groups. The intervention is focused on lowering the nighttime temperature of the home environment. Health and biometric data will be collected through a combination of physiological measurements, questionnaires, and biochemical measures taken at 3 time points during the hot season. Clinical outcomes include objective sleep behaviour, core body temperature, physical activity, blood pressure, blood glucose, anthropometrics, and body composition. Indoor and outdoor environmental data will be collected continuously using fixed indoor sensors and automatic weather stations. Housing and community characteristics, and socio-economic information will be collected. Quantitative comparisons will be made between intervention and control conditions using generalised linear mixed models. Qualitative data from consultive workshops will be used to assess the acceptability and feasibility of the adaptations.

**Discussion:**

Robust evaluation of the environmental and health outcomes of heat adaptations are limited for Africa, despite high climate vulnerability. HABVIA will address some of these gaps by assessing low-cost passive cooling interventions to promote heat resilience and improve health outcomes, providing real-world evidence for the feasibility of readily implementable and scalable adaptations in local contexts.

**Trial registration:**

Pan African Clinical Trials Registry (PACTR) PACTR202401521630856, version 1. Retrospectively registered on January 12, 2024.

**Supplementary Information:**

The online version contains supplementary material available at 10.1186/s12889-025-22757-6.

## Introduction

### Background and rationale

Temperatures across Africa are expected to rise at up to twice the rate of mean global temperatures, posing significant health threats to vulnerable communities [1]. Prolonged exposure to high day- and night-time temperatures has been implicated in a myriad of adverse health outcomes and has been associated with an increase in heat-related health risks across Sub-Saharan Africa (SSA) over recent decades [2]. Unfortunately, this trend is expected to do so even under the most ambitious emissions reduction scenarios [3, 4]. High ambient temperatures impact health both directly and indirectly [5–10]. Direct pathophysiological consequences include dehydration, increased burden on the cardiovascular system [11], and heat stroke, while warmer temperatures also indirectly impact health by increasing the risk of some infectious diseases and impacting food security [9]. Extreme heat has been associated with increased morbidity and mortality from conditions such as chronic kidney disease [8], respiratory disorders [6], adverse pregnancy outcomes [12], and compromised mental health conditions [13].

One proposed mechanism by which extreme temperatures may affect health outcomes is through disrupted sleep behaviour [14]. The role of sleep behaviour has recently gained traction as a key health indicator, underlying several biological functions implicated in the maintenance of cardiometabolic and mental health, immunity, and cognitive functioning [15]. Various dimensions of sleep behaviour, including sleep quality, sleep duration that is either too short or too long [16], mistimed sleep, and waking activity [17] have been associated with increased risk for the development of non-communicable diseases such as cardiovascular disease, obesity, diabetes, and depression [18–20].

The thermal environment also has important implications for sleep, as high temperatures can disrupt the thermoregulatory processes underpinning sleep onset and maintenance [21]. The effects of high radiant and air temperatures and humidity reduce the capacity for the body to cool itself via vasodilation and sweating [22], promoting wakefulness [23]. Additionally, residual effects of heat stress, cardiovascular strain and dehydration from exposure to high daytime temperatures can impact nocturnal decreases in core body temperature, disrupting sleep-wake cycles [9]. Notably, an emerging body of evidence suggests that higher outdoor or indoor temperatures are negatively associated with both sleep quality and quantity [24]. For example, a recent study pairing sleep observations from 68 countries and climate data found that increased night-time temperature delayed sleep onset and shortened sleep duration, thus increasing the probability of insufficient sleep [25]. These associations were stronger for residents of low-income countries and in hotter climates.

While humans are equipped with some capacity for physiological adaptation to heat exposure and changes in temperature through acclimatisation, this is limited by individual factors such as age, fitness-level, adiposity, and underlying chronic health conditions [26], as well as factors related to the external environment such as radiant temperature, humidity, and wind [22]. Achieving thermal comfort may therefore depend on heat adaptation interventions, such as passive cooling, that decrease exposure.

Passive cooling interventions that have successfully lowered indoor temperatures for occupants of urban informal settlements have been implemented in India, where various cool roof types have been shown to effectively reduce indoor ambient temperatures, compared to controls [27]. Regarding subsequent health outcomes, researchers in the United Kingdom have modelled the protective effect of external window shading to lower indoor temperature and decrease heat-related mortality risk [28]. In African settings, experimental testing of passive cooling interventions, using modelling methods and test cells, have included solar chimney height to maximise air velocity in Egypt [29], exterior coatings (texture and orientation) in Algeria [30], and solar shading, green roof, and reflective paints in Kenya [31].

While the results of these studies suggest a link between passive cooling interventions and reduced internal temperatures, the efficacy of these for improving human health outcomes has not been rigorously tested in non-laboratory conditions, in longitudinal cohorts, or using quantitative clinical measurements. Of the few reported heat adaptation interventions in SSA, many are modelling studies or are tested in artificial trial conditions and are not reflective of real-life circumstances [32, 33]. Therefore, robust evaluation of the environmental and health outcomes of heat adaptations in SSA Africa are critical, especially in real-world settings.

SSA, faces a widespread “adaptation deficit”, or lack of institutional, economic, and/or technological capacity to adapt to climate variability and weather extremes [34]. This adaptation deficit is juxtaposed against some of the hottest weather conditions across the globe, and a high extant burden of disease [35–37]. These factors disproportionally affect those living in informal and low-income settlements in SSA, where heat exposure is amplified due to urban heat island effects [38], inadequately cooled housing, and participation in livelihood activities and manual labour [39]. Climate services - easily accessible and disseminated climate information necessary for effective adaptation - are also sorely lacking in the region [40]. While there is growing evidence on the effectiveness of climate services in Africa [4, 41, 42], much of this is focused on drought, heavy rainfall, coastal and fluvial flood early warning. Heat early warning has received less attention. Although prototype heat early warning products are available [39] there has been little work on tailoring these products to the adaptation need and information access channels of specific vulnerable groups.

The lack of implemented heat adaptation in real-world settings in Africa poses a significant challenge to effective policy development and long-term climate adaptation planning for human health and well-being. This study primarily aims to explore the impact of passive cooling interventions in homes on key physiological and mental health outcomes, as well as on internal thermal conditions of buildings.

### Study aims and objectives

The HABVIA study aims to address some of the large evidence gaps in human health and wider social outcomes of heat adaptation in SSA, namely (i) the paucity of data from well-designed heat adaptation intervention trials in real-world high-vulnerability settings in the region and (ii) the absence of quantitative measurements of the health outcomes of these interventions. HABVIA aims to achieve this by identifying and implementing socially and culturally acceptable, affordable, and scalable heat adaptations for housing in low-income informal settlements in four communities in Ghana and South Africa.

Specifically, the following three objectives will be addressed:*Objective 1*. To explore the physiological response to extreme heat by quantifying the relationship between high seasonal ambient temperatures and humidity, and objectively measured health outcomes (primary: sleep; secondary: core body temperature, hydration) over three hot seasons in two rural and two urban African settings.*Objective 2*. To investigate any effects of passive-cooling interventions in lowering night-time indoor temperature and improving physical and mental health metrics, compared to controls.*Objective 3*. To determine the feasibility and social acceptability of such passive cooling adaptation interventions in climate vulnerable communities.

### Project team, partnerships and capacity building

HABVIA is part of the Wellcome Trust Heat Adaptation research programme aimed at testing and evaluating heat adaptation interventions to enhance public health in 11 low-and-middle income countries [43]. The collective efforts of the projects in this programme are designed to generate global evidence that will inform and support climate-health adaptation and policy development worldwide. Further HABVIA is collaborating with a diverse range of research partners including academic, governmental and policy makers as well as community outreach partners. The primary project team is a transdisciplinary team comprised of non-communicable disease and environmental health epidemiologists, human physiologists, climate scientists, heat-related policymakers, and climate service scientists ensuring a multidisciplinary approach to a complex problem. Underlying the success of HABVIA is the collaboration with often overlooked groups including a humanitarian/development non-governmental organisation, Slum Dwellers International. Capacity building of African health-climate researchers will be leveraged through the employment of post-graduate students, and the development of heat adaptation training seminars and field schools.

## Methods

The study methods will be reported in accordance with the Standard Protocol Items: Recommendation for Interventional Trials (SPIRIT) guidelines [44].

### Study design

HABVIA is a parallel-group controlled trial evaluating heat adaptation options in four sites, one urban and one rural low-income community each in Ghana and South Africa (SA), respectively. Participants will be assigned to intervention or control group using 1:1 block randomisation per site, with an equal distribution of male/females. An automated, computer-generated algorithm will be used for randomisation. Due to the logistical constraints of implementing adaptations in low-income settings, a building verification survey will be conducted to identify residences where the passive cooling interventions cannot be feasibly implemented. These participants will be automatically assigned to the control group and receive an alternative adaptation at the end of the study. Due to the nature of the interventions, participants and researchers will not be blinded to the intervention allocation. There are no pre-defined specific criteria for discontinuing the allocated interventions, but reasons for withdrawal will be tracked and reported in subsequent publications and taken into consideration for analysis.

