### Participants and enrolment

Participants were recruited from ongoing observational research activities from the following studies: 1) METS-Microbiome Study [45], being conducted in Nkwantakese, Kumasi, Ghana, and Khayelitsha, Cape Town, South Africa; 2) Heat, Health and Violence Study ([name] and [name], unpublished) in Mphego Village, Thohoyondou, South Africa; 3) Urban Health and Poverty Study and the Tsui Anaa Project [46] in Ga-Mashie, Accra, Ghana. Participants must be over the age of 18 years and live in one of the designated study communities. The following exclusion criteria apply: individuals with current symptomatic infectious diseases (particularly those inducing fever); pregnant or lactating women; persons with conditions preventing normal physical activities, e.g., lower extremity disability, and persons unwilling to implement the adaptation interventions. During the regularly scheduled research visits for their respective ongoing studies, potential participants were given information about the HABVIA study. A short screening tool was used to assess eligibility and potential interest in participation. At each of the study sites, 60 participants (*N*= 30 intervention and *N*= 30 control) were enrolled prior to the baseline measurement period in year 1 with additional recruitment and enrolment occurring in year 2 to account for drop-out.

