### Data analysis

For the statistical analysis, means and standard deviations will be presented for continuous variables; medians and interquartile ranges will be reported for continuous variables with asymmetrical distributions. Continuous variables with a small number of ordered categories, as well as all nominal variables, will be described with counts and percentages.Objective 1. The effect of ambient outdoor and indoor temperature on physiological health outcomes (primary: sleep; secondary: core body temperature, hydration) will be assessed both cross-sectionally and longitudinally using a univariable and multivariable generalized linear mixed model. For the multivariable model we will adjust for environmental conditions (humidity, cloud cover, wind speed, precipitation); health covariates (body composition, blood pressure, physical activity, glucose); participant characteristics (sex, age); household characteristics (roof and wall type; size) as well as differences between sites (country, rural vs. urban).Objective 2. The impact of the interventions will be tested in phases, first the association between intervention exposure and night-time indoor temperature, adjusting for household characteristics, site and intervention type. Secondly, the association between intervention exposure and sleep, our primary outcome as well as secondary physical and mental health outcomes. The mediating effect of night-time indoor temperature on this association will be investigated, while adjusting for the covariates described under Objective 1). In addition to this, structural equation modelling (SEM) will be used to produce a pictographic representation of a-priori determined relationships between the variables of interest. It does this by estimating path equations simultaneously allowing for the calculation of direct, indirect and total effects. For missing data, we will explore different imputation methods and run sensitivity analyses to explore whether participants lost to follow-up differ when compared to those who completed the study measurement periods.Objective 3. Qualitative data analysis will be done in parallel with the community engagement workshops and Focus Group Discussions, allowing emerging analysis to shape subsequent implementation and data collection procedures. The analysis will answer process evaluation questions and draw on various qualitative methods including but not limited to reflexive thematic analysis and codebook analysis. A qualitative analysis software (such as MAXQDA) will be used by the investigators to facilitate coding, data management, and data interpretation.

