## Discussion

Despite high vulnerability to heat-related health risk, few robust evaluations of the environmental, health and socio-economic outcomes of heat adaptations in real-world settings have been done in Africa. Indicating a dire need for reliable heat-health data and heat adaptations that are acceptable and feasible in local contexts. By addressing these gaps using extensive physiological measures, linked to environmental changes, the knowledge generated through HABVIA may help to inform policy to support the effective implementation of heat adaptations in sub-Saharan African settings, where they are sorely needed.

The controlled trial described in this protocol will explore whether passive cooling interventions impact on indoor ambient temperatures, particularly at night, and the extent to which they affect sleep quality and subsequent health outcomes. The limitations of this study include blinding issues, as it is not feasible to blind either participants or researchers to the intervention due to the highly consultive nature of the research as well as potential selection bias due to the leveraging of on-going cohorts. The study design is otherwise optimized for both internal and external validity by staggering monitoring periods, measuring potential confounders across health, climate and infrastructure, and by comparing group differences at both the cross-sectional and longitudinal endpoints.

As global warming progresses so will the need to build local capacity to respond and adapt to heat-related health issues in Africa. HABVIA aims to contribute to this by providing a multidisciplinary platform for climate-health research, education, and policy. In addition, the study’s commitment to community engagement for the design and implementation of the intervention, and the resulting mixed-methods approach, will allow for in-depth interpretation of the intervention outcomes and improve relevance and acceptability. Ultimately, the impact of these interventions will depend on uptake, by using locally sourced materials and generating site specific climate and social data that considers baseline health profiles, where pre-existing conditions may make people more vulnerable to heat stress, HABVIA is working towards tailored solutions for multi-vulnerable communities. This can also provide a framework for intervention development in future climate-related studies.

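### Homes that fail the building survey go automatically to control, so the control arm is partly non-randomised and the Objective 2 contrast can be confounded by dwelling

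*Protocol article*

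**What the plan says.** The Study design section gives the allocation as "Participants will be assigned to intervention or control group using 1:1 block randomisation per site, with an equal distribution of male/females", produced by a computer algorithm. It then adds that "a building verification survey will be conducted to identify residences where the passive cooling interventions cannot be feasibly implemented", and says of the people living there: "These participants will be automatically assigned to the control group and receive an alternative adaptation at the end of the study". It does not say what makes a home infeasible, how many are expected, or whether the survey comes before or after randomisation.

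The Participants and enrolment section gives 30 intervention and 30 control participants per site, who "were enrolled prior to the baseline measurement period in year 1", with further recruitment in year 2 to cover drop-out. The Research procedures section has the interventions put to participants in workshops after that baseline.

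For Objective 2, the Data analysis section first relates the intervention to night-time indoor temperature. It then examines "the association between intervention exposure and sleep, our primary outcome", with indoor temperature as a mediator. The household covariates named are roof type, wall type and size. Nothing there sets the auto-assigned participants apart.

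The Monitoring section calls the study a randomised trial. The Discussion gives lack of blinding and recruitment from existing cohorts as limitations, and continues: "The study design is otherwise optimized for both internal and external validity".

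**The concern.** Randomisation protects the comparison only for people who could have been allocated to either arm. Someone whose home fails the survey has probability zero of receiving the intervention, yet counts as a control. This holds whether the survey precedes or follows the random draw.

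The selection variable is also close to the outcome. It is a property of the dwelling, the first Objective 2 outcome is the temperature inside that dwelling, and that temperature is the proposed path to sleep. The section on residential data itself treats features of the dwelling and its surroundings as relevant to building temperature. If infeasible homes run hotter or cooler than feasible ones, the difference enters the contrast and can pass for, or hide, an intervention effect.

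The protocol deals differently with a similar problem. People unwilling to implement the adaptation are excluded altogether, which affects both arms alike. Homes unable to take it are kept, but on one side only.

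**Working it through.** **Inputs.** From the article: 60 participants per site, 30 per arm, four sites; 24 per group before attrition; 11.6 minutes of sleep associated with 4.3 °C. Not in the article, so assumed: f, the share of homes that fail the survey, and D, the mean difference between infeasible and feasible homes.

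**The plan's own figures.** 24/(1 − 0.20) = 30, so recruiting 30 per arm implies 20% attrition; the rate is not stated. The 24 cannot be reproduced independently, because no SD is given. With two-sided alpha 0.05, 80% power and the normal approximation, it corresponds to an SD of 4.3/[(1.960 + 0.842) × √(2/24)] = 5.32 °C.

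**Make-up of the control arm, per site.** The article does not say how the rule fits with 30 per arm, so two cases are needed.

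- Case A, feasible homes split 1:1: intervention = 30(1 − f), control = 30(1 − f) + 60f, non-randomised share s = 60f/[30(1 − f) + 60f] = 2f/(1 + f).
- Case B, arms held at 30/30: s = 60f/30 = 2f, and the feasible homes are no longer split 1:1.

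| f (assumed) | Infeasible homes | A: intervention / control | A: s | B: feasible homes, intervention / control | B: s |
|---|---|---|---|---|---|
| 10% | 6 | 27 / 33 | 6/33 = 18% | 30 / 24 | 6/30 = 20% |
| 20% | 12 | 24 / 36 | 12/36 = 33% | 30 / 18 | 12/30 = 40% |
| 30% | 18 | 21 / 39 | 18/39 = 46% | 30 / 12 | 18/30 = 60% |

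**What this could do to the contrast.** Without adjustment for baseline or covariates, the control mean shifts by s × D.

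- In minutes, purely as illustration with D = 11.6: case A gives 0.182 × 11.6 = 2.1, 0.333 × 11.6 = 3.9 and 0.462 × 11.6 = 5.4. Case B gives 2.3, 4.6 and 7.0. The sign is unknown.
- In SD units, case A, f = 20%, D = 0.5 SD: shift = 0.333 × 0.5 = 0.167 SD. At one site the standard error is √(1/24 + 1/36) = 0.264, the ratio is 0.63, and the two-sided type I error is about 10%. Over four sites it is √(1/96 + 1/144) = 0.132, the ratio is 1.26, and the error is about 24%.
- With f = 10% and D = 0.5 SD, the shift is 0.09 SD and the error about 6% at one site and 11% over four.

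These error rates ignore repeated measures and all adjustment.

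**The case against.** The strongest reply is the baseline season. Everyone is measured in the 2023–2024 hot season, before any adaptation, and again in two later seasons. A housing difference that is constant over time cancels in a change from baseline, and the Discussion mentions both cross-sectional and longitudinal comparisons. The models also adjust for household characteristics, and the dwelling survey collects more than roof, wall and size: windows, doors, ventilation, density and shading among others. This stands as mitigation. It is not a cure. The Objective 2 text does not state adjustment for the baseline outcome, and a home that heats differently may respond differently to a hotter or cooler season. Covariates deal only with what is measured.

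A reader might infer several stronger things that the document does not support:

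- That infeasible homes belong to poorer or less healthy people. The article gives logistical constraints as the background to the survey and does not say which buildings fail.
- That these homes have no counterpart in the intervention arm on the measured covariates. The arms may overlap on roof, wall and size if homes fail for other reasons.
- That people were moved to control after allocation. The order of enrolment, baseline and workshops makes this possible, but neither the survey nor the randomisation is dated.
- That the arms must end up unequal. The stated 30/30 per site, with later recruitment, allows case B.
- That modelling exposure means an as-treated analysis. The term is not defined, and analysis sets commonly sit in the SAP, which is not shown.
- That sleep is biased by a known number of minutes. Both f and D are assumed.

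**Conclusion.** The point holds in this form: by its own printed rule, the trial has a control arm that is partly non-randomised and contains homes that could never enter the intervention arm. No separate handling in the Objective 2 analysis is described, and the rule is not disclosed as a limitation. Because selection is on the building and the outcomes are indoor temperature and sleep, the contrast can be confounded.

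That conclusion needs no assumption about f. The size does: 18% to 46% of control (case A) or 20% to 60% (case B) for f between 10% and 30%. If few homes fail, the effect is small. Direction and residual bias after adjustment cannot be determined from the article.

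**What to change.** 1. Define the primary Objective 2 comparison as participants whose dwellings meet the same feasibility criteria in both arms, analysed by their computer-generated allocation.
2. Report auto-assigned participants as a separate non-randomised group, retained for Objective 1. Keep the comparison of all participants as a sensitivity analysis.
3. State, by site, how many homes failed, why, whether the survey came before or after randomisation, and the allocation ratio among feasible homes.
4. Add the rule to the limitations in the Discussion.
5. For any allocation still to come, survey first and randomise only homes that pass. The Trial status section has recruitment concluding in September 2024, so this may no longer be possible for those enrolled.

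**Cost.** Feasibility must be judged for control homes by the same criteria and without sight of outcomes. The planned survey of every participant's dwelling should supply most of this; where it is missing, or where only homes allocated to intervention were checked, it has to be completed. The control group shrinks and precision falls. With the back-solved SD, case A and 20% attrition, single-site power for the temperature effect is about 76%, 71% and 65% at f = 10%, 20% and 30%, against 80% by construction with no infeasible homes. Pooling over sites would soften this.
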